**Fig. 2 Fig2:**
[figure not shown]
Early lactation stimulation programme. *If OMM < 20 ml/day, cessation of HMA until improvement of milk supply. OMM, own mother’s milk; CLC, certified lactation consultant; HDM, human donor milk; HMA, human milk analyses

### Assignment of interventions: allocation

#### Sequence generation {16a}

The allocation sequence will be computer-generated by a statistical team member who will inform the researchers about the designated study group. Block randomization with stratification by delivery mode will be implemented. Patients will be randomly assigned to standard or tailored enteral nutrition fortification in 1:1 ratio. The block size will be variable and concealed until primary endpoint analyses.

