## Methods: participants, interventions, and outcomes

### Study setting {9}

The study will be carried out in three different sites (2 separate neonatal departments within the Medical University of Warsaw, and the Neonatal Department of the Wroclaw Medical University). All study sites are level III teaching hospital with approximately 2500–3000 (100 ≤ 32 weeks of gestation) deliveries per year. The local protocol is based on standard fortification of OMM and DHM. However, the staff is willing to implement new procedures in order to improve neonatal outcome. This should improve trial recruitment and adherence. The current OMM feeding rate during hospital stay in infants born at < 32 gestational age (GA) is 80%.

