### Sample size {14}

The sample size required to compare two means in two-sided equality test was estimated based on results from a prior double blind, randomized clinical trial, investigating the effect of TG vs SF of breast milk on the changes of anthropometric parameters and body composition in preterm children [23, 24]. It was determined that a mean difference of weight gain 1.9 g/kg/day between groups would be clinically important and feasible during intervention.

The following assumptions were made for the calculation: type I error (α) 5%, power 80%, equal sample sizes in both groups, the mean weight gain in the standard fortification group 19.3 g/kg/day, and the mean weight gain in the target fortification group 21.2 g/kg/day. To account for the higher uncertainty in measured weight gain due to differences between the studied and the quoted trial population, standard deviation value taken from the prior trial was increased by 50% to 3.75.

An estimated minimum size of each group is 68. Accounting for a presumed 20% attrition rate, due to potential dropouts, deviations from the protocol, and loss to follow-up, a minimum sample size required was estimated at 156 infants or 78 infants per treatment arm.

However, in order to detect a difference of 5 points in cognitive score of Bayley-III (secondary outcome) at 12 months of age (mean of 100 points, standard deviation (SD) 12) between the study groups with a power of 80% and α = 0.05, we have decided to increase the sample to 91 infants in each study group.

In summary, allowing for 10% of loss to follow-up, the target number of 200 premature infants will be recruited.

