### Statistical methods

#### Statistical methods for primary and secondary outcomes {20a}

Baseline characteristics will be presented for all included neonates in intention-to-treat and per-protocol analysis sets, by treatment group. Dichotomous variables will be presented as frequencies, categorical variables as median and interquartile ranges, and continuous variables as mean and standard deviations, along with 95% CI. In cases of missing data, i.e. due to adverse events or dropouts, in follow-up analysis, a weighted average taking account of changes in the gender ratio will be applied. Continuous variables will be tested against normality of distribution and the equality of variances between groups. For continuous variables distributed normally, the differences in means will be tested using *t* test; for continuous variables not distributed normally and for categorical variables between groups, comparison will be performed using the Mann-Whitney *U* test. The primary outcome will be assessed with one-tailed unpaired two-sample *t* test for noninferiority. Secondary and safety outcomes will be tested for two-sided superiority. Proportions of dichotomous variables will be tested using chi-square or Fisher’s exact test, whichever appropriate. In addition, the risk ratio (RR), the odds ratio (OR), and the number needed to treat will be assessed. For secondary outcomes, the difference will be considered significant when *p* value calculated in statistical tests will be < 0.05 or when the 95% CI for the mean difference will not include 0, or 1 in case of RR or OR.

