#### Methods for additional analyses (e.g. subgroup analyses) {20b}

Given the homogeneity of our study groups, we do not plan to conduct any subgroup analyses.

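### Allocation is stratified by delivery mode, but the fixed analysis is an unadjusted t test that ignores the stratum and the baseline covariates: valid but conservative, and it gives up precision

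*Protocol article*

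**What the plan says.** Sequence generation {16a} of the protocol article specifies: "Block randomization with stratification by delivery mode will be implemented". Delivery mode is the only stratification factor named. Study setting {9} says "The study will be carried out in three different sites", but site is not a stratum.

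Statistical methods {20a} gives the primary analysis as follows: "The primary outcome will be assessed with one-tailed unpaired two-sample *t* test for noninferiority". For normally distributed continuous variables generally, "the differences in means will be tested using *t* test". Other comparisons use the Mann-Whitney, chi-square or Fisher test. No model adjusted for a stratum or covariate appears. Regression is mentioned only in section {20c}, for filling in missing values. Sex enters only through a weighted average for missing follow-up data in {20a}.

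The remaining covariates are available at entry. Gestational age is an inclusion criterion, birth weight is needed for the small-for-gestational-age exclusion, and site is known for every infant.

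**The concern.** Stratified blocks force the arms to be nearly balanced on delivery mode. This removes the between-stratum component from the true sampling variance of the difference in means. A plain t test does not know this: it leaves the between-stratum spread in its pooled variance and reports a standard error that is too large. The trial takes on the complexity of stratifying and does not collect the benefit.

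Gestational age, birth weight, sex and site were not used to stratify, so leaving them out does not bias the standard error. It leaves explainable variation in the residual. Eligibility covers all gestations up to 32 weeks, and the intervention runs to 37 weeks post-conception or discharge, so length of exposure itself depends on gestation at birth. Outcomes {12} also expresses weight gain in grammes per week, a scale on which body size would be expected to add variance. At stake is precision for the primary outcome and, more noticeably, power for the 12-month Bayley score that set the final sample size.

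**Working it through.** **Inputs from Sample size {14}.** "The sample size required to compare two means in two-sided equality test"; "type I error (α) 5%, power 80%, equal sample sizes in both groups"; "a mean difference of weight gain 1.9 g/kg/day between groups would be clinically important". SD for weight gain is 3.75 g/kg/day. For Bayley cognitive score, the difference is 5 points and the SD is 12. Planned size is 91 per arm, raised to 200 in total for 10% loss. Section {18b} projects loss of at most 20% a year.

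**Assumed.** The share of outcome variance explained by delivery mode, or by all covariates together (R²). The document gives no value.

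**Reproducing the plan's figures.** n per arm = 2(1.960 + 0.842)² × SD² / difference².
- Weight gain: 2 × 7.849 × 3.75² / 1.9² = 61.1, so 62 per arm. The stated 68 does not reproduce, but the stated 78 after attrition does follow from 62 (62 / 0.8 = 77.5). This mismatch is a separate matter and does not affect what follows.
- Bayley: 2 × 7.849 × 12² / 5² = 90.4, so 91 per arm, as stated. By the exact t calculation, 91 per arm gives 79.8% power.

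**Step 1: effect of ignoring the stratum.** With the stratum balanced, the true SE is about √(1 − R²) times the SE that the t test reports. Actual two-sided level = 2[1 − Φ(1.96 / √(1 − R²))].

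| R² of delivery mode (assumed) | 1.96 / √(1 − R²) | Actual level |
|---|---|---|
| 0.02 | 1.980 | 4.8% |
| 0.05 | 2.011 | 4.4% |
| 0.10 | 2.066 | 3.9% |
| 0.20 | 2.191 | 2.8% |

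A simulation agrees in direction and approximate size. It used 91 per arm, permuted blocks within stratum, 4,000 runs, and assumed block sizes of 2, 4 and 6 with a 70:30 stratum split. At R² = 0.10 the level was 3.8% unadjusted and 5.0% adjusted. At R² = 0.20 it was 2.2% and 4.5%.

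**Step 2: precision from baseline covariates.** Residual SD = SD × √(1 − R²), and SE = residual SD × √(2/n). At 91 per arm the unadjusted SE for weight gain is 3.75 × √(2/91) = 0.556 g/kg/day. It falls to 0.527, 0.497 and 0.465 at R² = 0.10, 0.20 and 0.30. Two-sided t-test power at α = 0.05:

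| R² (assumed) | Weight gain, 91 per arm | Bayley, 91 per arm | Bayley, 80 per arm |
|---|---|---|---|
| 0 | 92.5% | 79.8% | 74.5% |
| 0.10 | 94.8% | 83.8% | 78.8% |
| 0.20 | 96.7% | 87.8% | 83.4% |
| 0.30 | 98.2% | 91.6% | 87.9% |

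The 80 per arm is 100 per arm (half of 200) less 20%, using the annual loss in {18b} up to the 12-month visit.

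All figures are two-sided, as in the sample-size section, and on the g/kg/day scale used there. The one-tailed noninferiority wording in {20a} conflicts with that section and needs its own resolution.

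**The case against.** The strongest reply is that nothing here is invalid. The only standard-error fault errs on the safe side, and if delivery mode explains just 2–5% of variance the level is 4.8–4.4%. Primary power is already 92.5% at 91 per arm two-sided, and about 96% one-tailed. The R² values have no support in the document, and covariate lists often sit in an SAP, which is not shown. Most of this stands, and it limits the size of the point. It does not remove it: the article names the primary test outright, so the mismatch with the allocation scheme is a stated method and not an omitted detail.

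Three stronger readings are tempting and are not supported.

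- **Twins inflate the type I error.** With 20–30% of infants in twin pairs and a correlation of 0.5–0.7 (both assumed), the level would be 6.2–7.5%, but only if siblings always share an arm. The document never mentions multiples, and {16a} describes random assignment of patients. Under individual allocation, sibling covariances cancel in expectation and the design effect is about 1.
- **Homogeneity was the reason for not adjusting.** Section {20b} reads "Given the homogeneity of our study groups, we do not plan to conduct any subgroup analyses". That explains the absence of subgroup analyses and says nothing about covariates.
- **Omitting site biases the comparison.** Milk from both arms goes to the same laboratory, so shared analysis gives no route to between-arm bias. Chance imbalance on site or gestational age is already covered by the unadjusted standard error. Adjustment would reduce it but corrects no error.

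**Conclusion.** The point holds as a mismatch between design and analysis and a loss of precision, not as a threat to validity. Ignoring the delivery-mode stratum makes the primary test conservative, by an amount that depends wholly on how strongly delivery mode predicts growth. Leaving out gestational age, birth weight, sex and site costs precision only.

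The gain for weight gain is modest: about 2 to 6 percentage points of power at 91 per arm for R² of 0.10–0.30. It matters more for Bayley, where power is 79.8% at the planned size and 74.5% if the projected 20% loss occurs. In that case an R² of 0.20 would bring it back above the planned 80%, while 0.10 would fall just short. These sizes rest on assumed R² values and on the plan's own differences and SDs.

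**What to change.** Before unblinding, replace the primary t test with a linear model containing arm, delivery-mode stratum, gestational age, birth weight, sex and site, and report the adjusted mean difference with its 95% confidence interval. Use the same covariates for the Bayley scores and body composition. Keep the unadjusted t test as a prespecified sensitivity analysis.

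The cost is a change of wording and slightly more analysis work. No extra infants or study procedures are needed, since the covariates are routine baseline data. With delivery mode in two categories and three sites, the model spends six more degrees of freedom out of about 180. The small downside is reliance on a prespecified model, so the form of each covariate should be written down in advance.

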#### Concealment mechanism {16b}

A member of the recruitment team will approach caregivers within the infant’s first 7 days of life. He or she will explain the study and obtain written consent for participating in the trial. Following this, the patient’s medical record number will be registered on a secure web-based platform and demographic data will be recorded. A study number together with the allocated treatment will be assigned by the platform.

#### Implementation {16c}

A member [a physician not involved in the patients care] of the research team will prescribe the allocated fortification on the patient’s drug chart. Milk fortification is routinely done twice a day (at 8 am and at 8 pm) for each following 12-h nursing shift (Fig. 1). For the purpose of the study, TF will be integrated in this schedule and performed by experienced registered nurses (RNs). The intervention will be performed by a RN blinded to treatment allocation. Patient’s data along with the result of the allocation will be sent to the statistical team. The randomization list will remain with the statistical team for the whole duration of the study.

All randomized infants who are prematurely discontinued from study will be considered *off study intervention/on study* and will follow the same schedule of events as those infants who continue study treatment. All of these infants will be followed through 36 months as scheduled. Once an infant is enrolled or randomized, the study site will make every reasonable effort to follow the infant for the entire study period. Participants may withdraw from the study for any reason at any time.

### Assignment of interventions: blinding

#### Who will be blinded {17a}

The bedside nurse, treating physicians, clinical psychologist, and data analysts will be blinded to the treatment allocation. Milk fortification will be performed in the milk bank by an experienced RN. Prepared milk portions will be transported to unit. Feeding portions from both treating arms will not differ in colour and structure.

#### Procedure for unblinding if needed {17b}

If unblinding is necessary, the actual allocation will only be disclosed to the treating physician. The investigator must report all code breaks (with reason) as they occur on the corresponding confidential recruitment file (CRF) page. Unblinding should not necessarily be a reason for study drug discontinuation.

### Data collection and management

#### Plans for assessment and collection of outcomes {18a}

##### Primary outcome

Weight gain velocity will be measured starting from the day infants regain their birth weight up to 4 weeks. Length and head circumference will be measured weekly until discharge and at 4 months of corrected age.

##### Secondary outcomes

Neurodevelopmental outcome:
12 months corrected age: BSID-III (Bayley Scale of Development Third Edition);3.5 years of corrected age: BSID and WPSSI-IV (Wechsler Preschool and Primary Scale of Intelligence, Fourth Edition IV).Behavioural problems: parental assessment by CBCL (Child Behaviour Check List) at 3.5 years corrected age.Feeding tolerance under whole period of fortification.Morbidity: NEC, ROP, BPD, IVH, PVL, sepsis, and pneumonia. Definitions provided in the “Outcomes {12}” section.

Time schedule of enrolment, interventions (including any run-ins and washouts), assessments, and visits for participants is presented in Table 2.

All data will be collected by the study personnel using electronic case report forms (e-CRF), developed specifically for the study. All data will be stored on a password-secured website. An introduction training session will be held at the beginning of the study for all study personnel at each study site.

#### Plans to promote participant retention and complete follow-up {18b}

All randomized infants who are prematurely discontinued from study drug will be considered *off study drug/on study*. They will follow the same participant timetable as those infants who continue study treatment. All of these infants will be followed through 36 months as scheduled.

Once an infant is enrolled or randomized, the study site will make every reasonable effort to follow the infant for the entire study period. It is projected that the rate of loss to follow-up on an annual basis will be at most 20%. Each study site staff will develop and implement local standard operating procedures to achieve this level of follow-up.

Participants may withdraw from the study for any reason at any time. The investigator also may withdraw participants from the study in order to protect their safety.

#### Data management {19}

All data will be entered electronically. Data integrity will be enforced through a variety of mechanisms. Referential data rules, valid values, range checks, and consistency checks against data already stored in the database (i.e. longitudinal checks) will be supported. Modifications to data written into the database will be documented through either the data change system or an inquiry system. Data entered into the database will be retrievable for viewing through the data entry applications. The type of activity that an individual user may undertake will be regulated by privileges associated with his/her user identification code and password. A complete backup of the database will be performed twice a month.

#### Confidentiality {27}

Complete patient and study information will be stored on a secure, password-protected, web-based platform. Only researchers involved in the study will be provided with a personalized login and password to access the study information. The statistical team will not have access to sensitive data such as date of birth, address, and contact details. All records containing the above patient details and relevant medical history will be stored separately in a locked file cabinet.

#### Plans for collection, laboratory evaluation, and storage of biological specimens for genetic or molecular analysis in this trial/future use {33}

We do not plan to perform any genetic or molecular analysis in this trial. Maternal milk samples will be labelled and stored in a separate refrigerator dedicated for biological material in the NICU. All left over samples of maternal milk will be destroyed as per hospital protocol for biohazard waste.

### Statistical methods

#### Statistical methods for primary and secondary outcomes {20a}

Baseline characteristics will be presented for all included neonates in intention-to-treat and per-protocol analysis sets, by treatment group. Dichotomous variables will be presented as frequencies, categorical variables as median and interquartile ranges, and continuous variables as mean and standard deviations, along with 95% CI. In cases of missing data, i.e. due to adverse events or dropouts, in follow-up analysis, a weighted average taking account of changes in the gender ratio will be applied. Continuous variables will be tested against normality of distribution and the equality of variances between groups. For continuous variables distributed normally, the differences in means will be tested using *t* test; for continuous variables not distributed normally and for categorical variables between groups, comparison will be performed using the Mann-Whitney *U* test. The primary outcome will be assessed with one-tailed unpaired two-sample *t* test for noninferiority. Secondary and safety outcomes will be tested for two-sided superiority. Proportions of dichotomous variables will be tested using chi-square or Fisher’s exact test, whichever appropriate. In addition, the risk ratio (RR), the odds ratio (OR), and the number needed to treat will be assessed. For secondary outcomes, the difference will be considered significant when *p* value calculated in statistical tests will be < 0.05 or when the 95% CI for the mean difference will not include 0, or 1 in case of RR or OR.

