#### Secondary outcomes

Growth (weight, length, head circumference) will be assessed at discharge and at 4 months of corrected age.Body composition (percentage of body fat, fat mass, fat-free mass) will be measured at discharge and at 4 months corrected age by air plethysmography (PeaPod).^1^Neurodevelopmental outcome:
12 months corrected age: BSID-III (Bayley Scale of Development Third Edition); the following stratification of index composite scores will be used in our study:< 70 (> 2 SD below the mean)—severe impairment70–84 (> 1 SD below the mean)—mild impairment≥ 85—normal development3.5 years of corrected age: BSID and WPSSI-IV (Wechsler Preschool and Primary Scale of Intelligence, Fourth Edition IV).Behavioural problems: parental assessment by CBCL (Child Behaviour Check List) at 3.5 years corrected age.Feeding tolerance under whole period of fortification.Morbidity: incidence of necrotizing enterocolitis (NEC), retinopathy of prematurity (ROP) and bronchopulmonary dysplasia (BPD), intraventricular haemorrhage (IVH), periventricular leukomalacia (PVL), sepsis, and pneumonia. Definitions provided below.

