##### Definitions

Feeding tolerance: defined as haemorrhagic residuals or vomiting bile until pathological causes are ruled out (intestinal obstruction or ileus) [17]. Gastric residuals and abdominal girth will not be checked routinely. Isolated green or yellow residuals will be considered unimportant.NEC (necrotizing enterocolitis): stage II or III. Stage II requires clinical manifestations of distended abdomen and radiological verification (intramural and/or portal gas). Stage III requires findings like in stage II and more severe clinical symptoms (shock, need for respirator). In surgery verified cases, no radiological verification is needed [18].ROP (retinopathy of prematurity): stages I to V, diagnosed by an ophthalmologist according to international criteria [19].BPD (bronchopulmonary dysplasia): need for oxygen, continuous positive airway pressure (CPAP), or mechanical ventilation at 36 + 0 weeks gestational age [20].IVH (intraventricular haemorrhage) [21].PVL [21].Early- and late-onset sepsis defined as a positive blood or cerebral fluid culture at less or more than 72 h of age, respectively [22].

Feeding tolerance has been chosen as an efficacy and harm outcome in order to evaluate whether TEN may impact milk absorption in the intervention group. Exclusive breastfeeding decreases the risk of NEC; however, the impact of TEN on the risk of developing NEC has not yet been studied. Blood culture confirmed early-onset sepsis (EOS) is a known risk factor for delayed implementation of EN and can impact the risk of late-onset sepsis (LOS). Diagnosis of EOS and LOS can be associated with intermitted withdrawal of enteral nutrition, BPD, IVH, and PVL which are markers of neonatal morbidity; hence, we decided to include them in our analysis.

Time schedule of enrolment, interventions (including any run-ins and washouts), assessments, and visits for participants is presented in Table 2.

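### Categorical variables are to be summarised by median and IQR, which conceals the spread across the Bayley-III impairment bands and has no meaning for unordered categories

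*Protocol article*

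**What the plan says.** Section {20a} of the protocol article sorts variables into three classes. The descriptive rule gives frequencies to dichotomous variables and presents "categorical variables as median and interquartile ranges"; continuous variables get mean and SD. On testing, it says that "for categorical variables between groups, comparison will be performed using the Mann-Whitney" U test. Two-level variables have their own rule: "Proportions of dichotomous variables will be tested using chi-square or Fisher’s exact test, whichever appropriate", with risk ratio, odds ratio and number needed to treat. As two-level variables are dealt with separately, the categorical class must consist of variables with more than two levels. Nothing in the section divides that class into ordered and unordered variables, and nothing assigns it counts or percentages.

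Three places elsewhere bear on what falls into that class:
- Outcomes {12}, Secondary outcomes, cuts the Bayley-III score at 12 months into three bands (below 70, 70 to 84, 85 and above), introduced by "the following stratification of index composite scores will be used in our study".
- Definitions describes ROP as "stages I to V, diagnosed by an ophthalmologist according to international criteria", although the outcome itself is listed as an incidence.
- Study setting {9} states "The study will be carried out in three different sites", so site is a natural unordered variable for a baseline table.

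**The concern.** A median and two quartiles describe a categorical variable badly when most infants fall in one category. All three figures then land in that category in both arms, and what happens in the adverse tail does not show. The Bayley bands are such a variable, because most infants are expected to score 85 or above. A table built to the written rule could print the same entry for two arms with clearly different rates of impairment, and a reader could not recover the counts from it.

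For unordered categories the problem is one of validity. A median category exists only once the categories are given an order, and a rank test on arbitrary codes tests those codes. The section states a rule that leads to both problems. It is a stated method, not a detail left for a later document, and an analysis plan that copied the sentence would carry it forward.

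**Working it through.** **Inputs.** From Sample size {14}: Bayley-III cognitive mean 100, SD 12, difference 5 points, power 80%, α = 0.05, 91 infants per group. From Outcomes {12}: cut points 70 and 85. Assumptions: scores are normal, and the lower arm has mean 95.

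**Reproducing the plan's figure.** n per arm = 2 × (1.96 + 0.842)² × 12² / 5² = 90.4, rounded up to 91. This agrees with the protocol.

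**Share in each band**, with Φ the standard normal distribution function:
- Below 85, mean 100: Φ((85 − 100)/12) = Φ(−1.25) = 10.6%.
- Below 85, mean 95: Φ((85 − 95)/12) = Φ(−0.833) = 20.2%. The ratio is 1.92.
- Below 70: Φ(−2.5) = 0.6% against Φ(−2.083) = 1.9%.

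**What the written summary shows.** The lower quartile leaves the top band only when more than 25% of an arm scores below 85. That requires an arm mean below 85 + 0.6745 × 12 = 93.1. Neither mean is that low, so each arm's expected median and IQR are all in the normal band.

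If the 5 points are taken upward instead (100 against 105), the shares below 85 are 10.6% and Φ(−1.667) = 4.8%. The summaries again agree.

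**At the planned size.** Take counts severe/mild/normal of 1/9/81 against 2/18/71. Impaired infants double from 10 to 20 of 91. The lower quartile is the 23rd lowest value, which is in the normal band in both arms, so the printed summaries are the same. In 4,000 simulated trials at 91 per arm with means 100 and 95, all three quartiles matched between arms in 85%.

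**What the written test shows.** For the same counts, Mann-Whitney (two-sided, tie-corrected, no continuity correction) gives p = 0.047. Over the simulated trials it rejected in about 45%, close to the 44% power of a comparison of two proportions below 85. The rank test therefore loses nothing important for these ordered bands.

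**Unordered categories.** The counts here are assumed, for illustration: categories A/B/C of 40/25/26 against 25/41/25. The Mann-Whitney p value depends only on the order in which they are numbered:
- A, B, C: p = 0.167
- B, A, C: p = 0.098
- A, C, B: p = 0.007

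Chi-square gives p = 0.025 whatever the numbering.

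**The case against.** The strongest defence is that no declared result is lost. The Bayley score is powered as a continuous variable, so the 5-point difference would be reported as means with SD and 95% CI and tested at about 80% power. The bands are an addition to that, and their prescribed rank test is sound. All of this stands. A reader might infer that the trial would report no difference in neurodevelopment; the document does not support that, because only the summary entry for the bands is affected.

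A reader might also infer that ROP severity would be concealed. The abstract, the secondary objectives and the outcome list all name the incidence of ROP, and the stages appear only in a definition. Incidence is yes/no and is already served by frequencies, chi-square or Fisher's exact test, and risk and odds ratios. The same holds for NEC, BPD and sepsis. The problem would reach ROP only if it were tabulated by stage.

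Nor would the summary hide any rise, however large. Tripling 10.6% gives 31.7%, which passes the 25% threshold and moves the lower quartile.

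On unordered variables, the protocol names no such outcome with more than two levels and states no test of sites between arms, so the coding problem has no declared outcome to act on.

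Finally, the descriptive sentence follows directly on one about baseline characteristics and could be read as governing baseline tables only. That would take the Bayley bands out of its reach, but it would leave them with no descriptive rule and would apply the median to baseline variables such as site, where it is meaningless. It is also possible that categorical was meant as ordinal. The text does not say so, and the summary would still be uninformative for the bands.

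**Conclusion.** The point holds as a minor error in a stated method. For the Bayley-III bands, the median and IQR would be expected to match between arms although impairment below 85 nearly doubles, from 10.6% to 20.2%. This rests on normal scores with SD 12, on reading the design difference as 100 against 95, and on both arms staying below 25% impaired. The fault there is the summary; the rank test and the continuous comparison are sound. For unordered variables, the summary has no meaning and the prescribed test, wherever applied, would depend on the coding. In this document that matters mainly for baseline descriptors such as site. The primary outcome, the sample size and the yes/no incidences are unaffected.

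**What to change.** In section {20a}, replace the rule for categorical variables with the following:
- Report every categorical variable as n (%) in each category, by arm.
- Keep the Mann-Whitney test for ordered categories such as the Bayley-III bands, and for ROP if it is reported by stage.
- Use chi-square or Fisher's exact test wherever unordered categories are compared.
- Reserve median and IQR for skewed continuous variables.

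A proportional-odds odds ratio with 95% CI could be added for ordered outcomes, but it is optional. The cost is one sentence and slightly longer tables, with no new data and no effect on the sample size.

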### Objectives {7}

#### Research hypothesis

Tailored fortification of enteral nutrition improves weight gain velocity of preterm infants born at ≤ 32 weeks of gestation compared to standard fortification.

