### Trial design {8}

The trial is designed as a randomized observer and patient blinded controlled multicentre superiority trial with two parallel groups with 1:1 allocation ratio.

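### The primary outcome is assigned a one-tailed non-inferiority test, although the hypothesis, design and sample size are all for superiority

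*Protocol article*

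**What the plan says.** Section {20a} of the protocol article, on statistical methods, fixes the primary test: "The primary outcome will be assessed with one-tailed unpaired two-sample *t* test for noninferiority". The next sentence treats the other outcomes differently: "Secondary and safety outcomes will be tested for two-sided superiority". The significance rule that closes the section (p below 0.05, or a 95% CI excluding the null value) is limited to secondary outcomes.

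The rest of the article describes a superiority trial:

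- Research hypothesis: "Tailored fortification of enteral nutrition improves weight gain velocity of preterm infants". The primary objective is put in the same terms.
- Trial design {8}: "controlled multicentre superiority trial with two parallel groups with 1:1 allocation ratio".
- Sample size {14}: "The sample size required to compare two means in two-sided equality test", with alpha 5%, power 80%, means of 19.3 and 21.2 g/kg/day and an SD of 3.75.

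No non-inferiority margin appears anywhere in the article. The only alpha that bears on the primary outcome is the 5% in the sample size section, where it belongs to a two-sided test.

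**The concern.** The sentence that governs the trial's main conclusion specifies a test of a different question from the one the trial asks. The non-inferiority null says that targeted fortification is worse than standard fortification by at least some margin. Rejecting it rules out that much harm. It does not show improvement, which is what the hypothesis and the primary objective claim.

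This is hard to read as loose wording. Two adjacent sentences contrast non-inferiority for the primary outcome with superiority for the others, so the primary outcome is held to a weaker standard than the secondary ones.

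The abstract's discussion says that targeted fortification may become a recommended first-line approach if it is shown to improve growth. A non-inferiority result could be reported as trial success without supporting that step. If the margin is settled only after the data are known, the choice of margin could decide the outcome.

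**Working it through.** **Step 1: which test does the sample size assume?** Inputs from Sample size {14}: difference d = 21.2 − 19.3 = 1.9 g/kg/day, SD = 3.75, alpha 5%, power 80%, equal groups.

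n per arm = 2 × (z_alpha + z_power)² × SD² / d²

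- Two-sided 5%: 2 × (1.960 + 0.842)² × 3.75² / 1.9² = 61.2, so 62 per arm (63 with the noncentral t).
- One-sided 5%: 2 × (1.645 + 0.842)² × 3.75² / 1.9² = 48.2, so 49 per arm.

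The article states 68 per group, which neither calculation gives. Its next figure does follow from 62: 62 / (1 − 0.20) = 77.5, so 78 per arm and 156 in total. Starting from 68 would give 85 per arm. The 68 is a separate discrepancy. For this point, what matters is that the stated 78 and 156 match a two-sided test and not a one-sided one.

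**Step 2: margin of 0.** The test becomes one-sided superiority. Taking the 5% in the sample size section as the one-sided level (an assumption), the chance of falsely declaring benefit is 5%. A two-sided 5% test gives 5% / 2 = 2.5% in that direction. At 91 per arm:

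- SE = 3.75 × √(2/91) = 0.556 g/kg/day.
- Observed difference needed, two-sided 5%: 1.960 × 0.556 = 1.09.
- Observed difference needed, one-sided 5%: 1.645 × 0.556 = 0.91.

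A one-tailed test in this direction also cannot declare targeted fortification worse on the primary outcome.

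**Step 3: margin above 0.** The article states none, so the margins below are assumptions. With true difference D and margin m, by the normal approximation:

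P(declare non-inferior) = Φ((m + D)/SE − 1.645)

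Results for 91 per arm, one-sided 5% and no true benefit (D = 0):

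| Assumed margin (g/kg/day) | m/SE − 1.645 | Probability of success |
|---|---|---|
| 0.5 | −0.75 | about 23% |
| 0.95 | 0.06 | about 53% |
| 1.0 | 0.15 | about 56% |
| 1.9 | 1.77 | about 96% |

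For the margin of 1.9, noncentral t results over a range of analysed numbers (200 recruited is 100 per arm; 10% loss leaves 90 and 20% loss leaves 80):

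| True difference (g/kg/day) | 80 per arm | 90 per arm | 100 per arm |
|---|---|---|---|
| 0 | 0.939 | 0.959 | 0.973 |
| −0.5 (targeted worse) | 0.760 | 0.802 | 0.838 |

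**Step 4: can the trial afford the superiority test?** Two-sided 5% power for 1.9 g/kg/day (noncentral t) is 89.0% at 80 per arm, 92.5% at 91 and 94.6% at 100.

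**The case against.** The strongest reply is that a journal article condenses the full plan, and that a margin and a one-sided alpha may stand in an analysis plan that is not shown. That is fair for the missing margin taken alone, and it means nobody can say that the margin will in fact be chosen late. It does not resolve the conflict. The article itself fixes a non-inferiority test for a superiority hypothesis, and supplying a margin would not make that test answer the hypothesis.

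Several narrower objections have some force:

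- With a margin of 0, or with a pre-specified step from non-inferiority to superiority, the analysis could show improvement. The article states neither, so the stated test fails to support the claim for any positive margin but not for every conceivable one.
- The doubling of the false-benefit rate depends on a one-sided level of 5%. At one-sided 2.5% with a margin of 0 nothing doubles.
- A margin of 1.9 is lenient, and smaller margins give much lower pass rates, as the first table shows. Even at 1.9, with 91 per arm, an observed difference below −1.9 + 0.91 = −0.99 g/kg/day would fail.
- Worse growth could still be found among the secondary outcomes, which are tested two-sided.

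These points limit the size of the effect. None of them reconciles the sections.

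**Conclusion.** The concern holds. The primary test in section {20a} contradicts the research hypothesis, the primary objective, the design statement and the sample size, and nothing in the article reconciles them. Followed as written with a positive margin, the test would not answer the trial's own question.

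The size depends on what is assumed for the unstated quantities. At one-sided 5% with a margin of 0, the false-benefit rate is 5% instead of 2.5%. With assumed margins from 0.5 to 1.9 g/kg/day, SD 3.75 and 91 per arm, a strategy with no benefit would be declared a success with probability from about 23% to about 96%. The contradiction itself rests on no assumption.

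**What to change.** Replace the primary-outcome sentence in section {20a} with wording such as: *The primary outcome will be tested for superiority at a two-sided alpha of 0.05 and reported as the between-arm difference in g/kg/day with its 95% CI.* Delete the one-tailed and non-inferiority wording, and make any separate analysis plan agree.

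A one-sided superiority test at 0.025 would give the same error rate in favour of targeted fortification. The two-sided form is preferable because it matches the sample size section and can also show a difference in the other direction.

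The suggested wording uses g/kg/day because the trial is powered on that scale. The Outcomes section gives grammes per week, a separate discrepancy that should be settled at the same time.

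The cost is one sentence, changed by amendment before unblinding. No extra infants are needed: a two-sided test requires 62–63 per arm for 80% power, and the planned numbers exceed that.
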